**Figure 1 Fig1:**
[figure not shown]
Social ecological framework for understanding exercise determinants.

**Table 2 Tab2:** **Education topics**

Education topics	Key points
1) Introduction to Exercise	• Benefits of Physical Activity
	• Program targets 3 areas of PA (aerobic, resistance, and flexibility)
	• PA is safe, feasible and has shown to provide benefits
2) Goal Setting	• Goal setting will assist with your dedication and motivation to complete the exercises
	• SMART Goals - Specific, Measurable, Attainable, Realistic, Timely
	• Use the goal worksheet in the manual
	• Make long term and short term goals
3) Behavior Change	• The plan you set out may not be followed 100%
	• Anticipate obstacles that may come as you are changing a behaviour and develop strategies for dealing with it before it arises
	• Monitor your progress, Reward yourself, Visualize your success
4) Planning for Barriers	• Biggest perceived obstacles
	○ Lack of time, self-discipline, partner and ability
	• Plan ahead for periods of inactivity
5) Social Support	• You are more likely to be successful if your family, friends and even co-workers are supportive of you
	• Social support can occur in many forms – encouragement, completing activities with you, etc.
6) Monitoring Behavior	• Mix up your activities to stay motivated
	• Try something new, or something you have done previously
	• It is very easy to enter an exercise rut
7) Maintaining Motivation	• Greatest source of motivation: Fun/enjoyment/stimulation, feeling of accomplishment, pleasure of learning and benefits (i.e. improved sleeping)
	• Pursue something that you enjoy, that is convenient to your schedule
	• Take opportunities to be active
8) Personal Control	• Believing that you are in control of your own life give you reinforced motivation and further commitment to make changes
9) Self- Discipline, Reward & Attitude	• Self-discipline can result in increased productivity, improved self-esteem and confidence
	• Rewards – use workbook in manual
	• Attitudes toward change can determine whether you will be successful
10) Adapting your Program	• Adapting your program – FITT principle
11) Health and the Media	• Be mindful of the ‘Get fit quick’ media marketing – Health eating and regular PA will help maintain a long-term health lifestyle
12) Lifelong Active Living	• Use some of the tips and tricks in the manual to assist with continuing your active life
	• Change things up, work towards small goals, work with a friend, etc.

The 10-point Rating of Perceived Exertion (RPE) scale is used to monitor exercise intensity levels [52], with participants instructed to maintain their intensity level at 3–6 during exercise sessions. RPE levels are related to target HR, as it corresponds to the linear change in HR [53]. HR monitors (Polar, NY, USA) are used at 3-week intervals during the exercise sessions across all intervention arms. This is to ensure participants maintain appropriate heart rate levels during the session, ensuring calibration with the 3–6 rating on the RPE scale throughout the intervention period. Home-based participants are trained to use HR monitors which are provided to them. Participants in the supervised 1:1 and group programs will have staff present to assist in HR measurement.

Study staff will hold monthly conference calls and staff will be trained on testing and training procedures, to ensure standardization across both sites. Supervised exercise sessions are documented with standard forms at all sites.

### Progression

Participant progression is individualized, and monitored by a CEP or health coach every three weeks to ensure that progression is occurring. The participant’s intensity level during the exercises sessions (both aerobic and resistance) will be used as an indicator of whether the participant is ready to progress. CEPs or health coaches adjust intensity levels to ensure participants maintain the desired intensity range throughout each exercise session. Documentation of this progression is completed using a standard form across all arms of the intervention and both study sites. Participants who are working below their target HR when performing aerobic exercise will first increase their exercise duration (i.e., from 15 to 20 minutes), followed by an increase in exercise intensity (i.e., increase walking speed or grade). Similarly, participants who are able to complete ≥12 repetitions and 3 sets of a specific resistance exercise will increase the resistance (i.e., blue band to purple band; next resistance level) they are performing the exercise at to ensure that they are continuing to progress effectively throughout the program.

### 1:1 supervised training

Participants in the 1:1 supervised training complete three sessions per week with a CEP for a period of six months, and are encouraged to perform one to two additional weekly independent (home-based) sessions. Each exercise session consists of cardiovascular training for 15 to 30 minutes, resistance training exercises (working major muscle groups), and flexibility training (including 5–10 minutes of stretching at the end of each session). All participants are provided with resistance bands for home use.

### Group supervised training

This protocol differs from the 1:1 training protocol in only one way: a group of 4–6 individuals are supervised by a CEP at each session.

### Home-based training

The same protocol and training frequency as the 1:1 and group supervised training program is explained and recommended to be followed by the home-based smartphone-assisted participants. Along with the resistance bands provided, participants in the home-based training group also receive a stability ball, an exercise mat, a HR monitor (with instructions), and a smartphone with a 6-month paid phone and data plan. Participants in the home-based arm complete an orientation session with a CEP prior to the commencement of the training. Participants are oriented to the same exercise manual that is provided to the supervised group participants, and review the resistance and flexibility exercises with a CEP to ensure proper technique. During the orientation participants also meet with the health coach to review the smartphone application and the role of the health coach. Remote health coaches and smartphone technology are intended to provide support to participants in the home-based training program during the intervention phase, as there is no direct (i.e. face-to-face) supervision with this group. The health coach connects with participants on a regular basis (ideally once each week) to follow up on the week’s exercise sessions and to provide guidance for the participants and assist with any smartphone application issues. Health coaches instruct the participant when to use the HR monitors to evaluate intensity every three weeks. A customized smartphone application is used (Connected Wellness Platform) that allows users to input health information, levels of symptoms, and exercise routines, as well as tracking progress over time.

### Tapering

#### Supervised sessions

Tapering allows participants within the supervised training arms to transition from predominately supervised training to independent exercise training. This is in place to encourage participants to continue to exercise independently at the same intensity and frequency as achieved during their supervised exercise programs. Tapering occurs for participants in the 1:1 supervised and group-based training arms. Starting in month five, supervised sessions are reduced to two sessions per week. In the final month (month six), supervised sessions are tapered further to one session per week. Participants are encouraged to replace the supervised sessions with equivalent independent exercise sessions.

### Health coach support

For the home-based group, a similar concept of tapering will be introduced to reduce the level of support provided by health coaches. In the first four months the health coaches will contact each participant once every week and will be available seven days per week, with turnaround time within an hour. In the final two months of the intervention, the health coaches will contact each participant once every two weeks and will be available five days a week. Text message turnaround time will be reduced from within the hour to next day.

### Safety

The CEP reviews with each participant precautions and safety while exercising during the participant manual orientation and participants are reminded to review the manual prior to commencing independent exercise sessions. All exercise trainers have cardiopulmonary resuscitation (CPR) and automated external defibrillator (AED) training and have received safety training at each site. Any adverse events are document using the National Cancer Institute common terminology criteria for adverse events v4.0 [54].

### Cost-effectiveness analysis

This phase II study investigates the feasibility of completing a phase III trial and a full companion economic evaluation. In the phase II design there will be no formal cost-utility analysis, however outcomes relevant to economic analyses regarding health status will be collected at each assessment time point using a generic utility instrument (the European QOL 5-dimension measure (EQ-5D)) [55]. Costs are captured with a patient-reported diary that has been used in prior studies of men with PC [56,57]. Costs related to health care utilization (e.g. visits to a physician or physiotherapist), transportation, purchase of exercise equipment (including gym membership fees), and related costs are captured at each of the five time points where QOL and fitness data are captured.

### Sample size calculation/power

Following standard guidelines for a phase II RCT [58-60], we have targeted 30 patients per arm (90 patients in total) to provide precise estimates of parameters related to the primary outcomes as well as important feasibility information that will be crucial to inform the phase III study. Assuming 10% drop-out, we will recruit 100 patients across both sites.

### Statistical analysis

Statistical analysis focuses on feasibility outcomes and those which will inform decisions about moving forward to and planning a phase III clinical trial. Feasibility outcomes include recruitment rates, and proportions of participants retained and adherent at landmark times throughout the study, all of which will be estimated with 95% confidence intervals. Additionally tallies are kept on reasons for not participating. Each participant also completes an exit interview and satisfaction survey which will be analyzed for participant satisfaction within the study and cost effectiveness analysis.

Adherence is assessed through the two different binary definitions given previously, based on steps or hours of exercise. We estimate proportions adhering to exercise in each three-month period and use generalized estimating equation logistic regression models to compare adherence between groups and assess predictors of adherence over the course of the study. Predictors include sociodemographic (e.g. age, education), clinical (disease stage), baseline fitness, and ecological variables (NEWS, etc.).

Quality of Life (FACT-G and FACT-P), musculoskeletal fitness, and aerobic fitness are efficacy outcomes that are analyzed using linear mixed effects model with subject-specific random effects and group-by-time interactions. The analysis will not focus on differences between groups, but, to assist with phase III trial design, estimation of measures of within and between-person variance.

As previously mentioned, there is no formal cost-effectiveness analysis, however data obtained (diary and EQ-5D completion and participant acceptance) is used to help develop this outcome for the phase III study. Descriptive estimates of costs by category and per intervention arm as well as per site (Toronto, Calgary) will be calculated.

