## Abstract

**Background:**

Androgen deprivation therapy is commonly used to treat prostate cancer, the most common visceral cancer in men. However, various side effects often worsen physical functioning and reduce well-being among men on this treatment. Based on existing evidence, both resistance and aerobic training provide benefits for this population yet adherence rates are often low. The method of exercise delivery (supervised in-center or home-based) may be important, yet few studies have compared different models. Additionally, long-term exercise adherence is critical to achieve sustained benefits but long-term adherence data and predictors of adherence are lacking. The primary aim of this phase II, non-inferiority randomized controlled trial is to determine whether three exercise training delivery models are equivalent in terms of benefits in quality of life and physical fitness in this population. Secondary aims include examination of long-term adherence and cost-effectiveness.

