Thus, the primary aims of this phase II non-inferiority RCT are:To determine the feasibility of conducting a large multi-center non-inferiority RCT of three exercise delivery models in men with PC on ADT. Feasibility outcomes include participant recruitment, retention, adherence, outcome capture, and satisfaction;To obtain preliminary efficacy estimates for (a) group-supervised in-centre, and (b) home-based (smartphone-assisted) supported exercise programs, compared to (c) a 1:1 supervised in-center exercise program study for the clinical outcomes of QOL and physical fitness, and to select a primary outcome for a subsequent phase III trial;To examine adherence to exercise and predictors of adherence in each exercise group during the 6-month intervention and for 6 months after program completion;To determine the feasibility of conducting an economic analysis comparing exercise interventions and usual care.

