### Adherence

Program adherence and predictors of adherence are assessed. Adherence measures include physical fitness outcomes (as the most proximal, objective outcome of exercise adherence), accelerometry, as well as attendance at exercise sessions (for those in supervised programs). For those in the home-based, smartphone-assisted arms, use of the self-report software (Connected Wellness Platform, NexJ Systems, Toronto, Canada) and interview responses (obtained by health coaches) will provide proxies for attendance and exercise program engagement. Accelerometers (Actigraph GT3X, Pensacola, FL) will be worn for seven days at each assessment time point. Accelerometers will be worn during waking hours, allowing for capture of total physical activity during the observation period [40]. Data will be extracted from the accelerometer in 60-second epochs and will be screened through; (i) at least 4 days of valid data, including (ii) at least 10 hours of wear time per day; (iii) non-wear time will be assessed as periods of time with no movement (0 counts per minute) for more than one hour at a time.

Two common definitions of adherence are adopted: 1) at least 150 minutes of MVPA per week, based on the ACSM guideline for cancer survivors [28] and the revised CSEP guideline for adults and older adults [41]; and 2) at least 10,000 steps per day [42] for 6+ days per week. In a sensitivity analysis, a recently described age-specific cut-off of 7,500 steps per day for older adults [43] is also tested. The accelerometer data will be analyzed by examining the total amount of MVPA and sedentary behavior during the 7 days. MVPA is defined as activity >1952 counts per minute [42] and sedentary behaviour as <100 counts per minute and time spent inclined.

Predictors of adherence are targeted based on a social ecological framework (Figure 1) [44]. Multiple potential determinants of exercise adherence and the inter-relatedness of these determinants are examined using brief validated measures at each level: exosystem (Neighborhood Environment Walkability Scale: Short Form (NEWS) [45]); mesosystem (Health Care Climate Questionnaire [46] and Related to Others in Physical Activity Scale [47]); and microsystem (Behavioral Regulations in Exercise Questionnaire-2 [48,49] and a Planning, Attitudes, & Barriers scale [50,51]).

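### Arm comparisons and predictor analyses of accelerometer-based adherence rest only on yes/no cuts; adding a model of MVPA minutes and daily steps would recover precision cheaply

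*Protocol article*

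**What the plan says.** The list of primary aims at the end of the Background section includes the following as its third item: "To examine adherence to exercise and predictors of adherence in each exercise group during the 6-month intervention and for 6 months after program completion". The abstract ranks part of this lower: "Secondary aims include examination of long-term adherence and cost-effectiveness".

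The Adherence section has accelerometers worn for seven days at each of the five assessments. It adopts two definitions of adherence, "at least 150 minutes of MVPA per week" and "at least 10,000 steps per day [42] for 6+ days per week", with 7,500 steps per day as a sensitivity cut. It adds: "The accelerometer data will be analyzed by examining the total amount of MVPA and sedentary behavior during the 7 days". It also names fitness outcomes as adherence measures.

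The Statistical analysis section then fixes the method. "Adherence is assessed through the two different binary definitions given previously, based on steps or hours of exercise". Proportions adherent are estimated for each three-month period, and the investigators will "use generalized estimating equation logistic regression models to compare adherence between groups and assess predictors of adherence over the course of the study". Linear mixed models with group-by-time terms are named in the same section, but for quality of life and for musculoskeletal and aerobic fitness.

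The section on criteria to move to phase III sets 70% for adherence. It allows an arm found inferior to the other two to be dropped, with adherence among the grounds.

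**The concern.** Weekly MVPA minutes and daily step counts are continuous. After the cut, a man at 145 minutes counts the same as a man at 0, and a man at 155 the same as a man at 400. The step rule is cut twice, first by day and then by number of days.

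This is a stated modelling choice, not a detail left to a fuller document. Logistic GEE on the cuts is named for both the arm comparison and the predictors, and no model is named for the continuous measures behind them.

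At stake is how well a trial of this size can describe activity differences between arms, and what drives them. The trial lists this aim as primary, and its arm results on adherence can affect which arms go forward. Eligibility sharpens the point. Men who already meet the guideline for MVPA are excluded, so most should start below the 150-minute cut. A yes/no baseline then says little, whereas a continuous one still separates inactive men from nearly adherent men.

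**Working it through.** **Inputs from the protocol article.** 30 men per arm, 90 in total; 10% drop-out; 100 recruited; 70% adherence criterion; assessments at baseline and at 3, 6, 9 and 12 months.

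**Assumptions, not in the document.** A normal activity scale with SD 1; a uniform shift of *d* SD between two arms; a two-sided 5% level; the share of men above the cut; the within-person correlation. The article gives no significance level, effect size, SD or power for adherence.

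**Step 1: the plan's own figure.** 90 / (1 − 0.10) = 100, which matches the stated recruitment. The stated rationale for 30 per arm is precise estimation and feasibility information, so there is no power figure to reproduce.

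**Step 2: information kept by the cut, one measurement.** Relative efficiency = φ(c)² / [p(1 − p)], where p is the share adherent, c = Φ⁻¹(p), and φ and Φ are the normal density and distribution function.

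| Adherent | φ(c) | Relative efficiency | 30 men carry the information of |
|---|---|---|---|
| 50% | 0.399 | 0.159 / 0.25 = 0.64 | about 19 |
| 70% | 0.348 | 0.121 / 0.21 = 0.58 | about 17 |
| 80% | 0.280 | 0.078 / 0.16 = 0.49 | about 15 |

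**Step 3: power at one visit, 30 per arm.** Take d = 0.5 and 70% adherent in the better arm.

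- Continuous: 0.5 × √(30/2) − 1.96 = −0.02, giving 49%.
- Binary: the other arm has Φ(0.524 − 0.5) = 0.51 adherent. The pooled proportion is 0.605, the null standard error is √(2 × 0.605 × 0.395 / 30) = 0.126, and the alternative standard error is 0.124. Then (0.19 − 1.96 × 0.126) / 0.124 = −0.46, giving 32%.
- Loss: 17 points.

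With 70% adherent in the better arm, other shifts give:

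| d | Continuous | Binary | Loss (points) |
|---|---|---|---|
| 0.4 | 34% | 22% | 12 |
| 0.6 | 64% | 44% | 20 |
| 0.7 | 77% | 56% | 21 |
| 0.8 | 87% | 68% | 19 |

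With 30% adherent in the better arm and d = 0.7, it is 77% against 44%, a loss of 33. Over d = 0.4 to 0.8 and 30% to 80% adherent, the loss runs from about 11 to 35 points. For d = 0.2 to 0.3 at the same adherence rates it is about 3 to 8 (10 if only 20% are adherent).

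**Step 4: repeated visits, which is what the plan describes.** Four post-baseline visits were simulated with latent correlation 0.5 and 0.7, cluster-robust standard errors, and d = 0.5 to 0.7. The loss was about 8 to 13 points with the better arm at 50% or 70% adherent, and about 17 to 22 at 30%. A separate four-visit GEE simulation, at correlation 0.4 and 0.7, agrees:

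- 70% against 50% adherent: 79.8% and 62.2% continuous, 66.8% and 50.7% binary; losses 13.0 and 11.5.
- 30% against 15% adherent: 76.7% and 62.8% continuous, 56.3% and 44.5% binary; losses 20.4 and 18.3.

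Averaging over visits recovers part of what a single cut loses, so Step 4 gives smaller losses than Step 3 for the same shift.

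**Step 5: predictors.** One predictor was assumed to correlate 0.25 with activity, with 90 men, four visits, and within-person correlation 0.5 and 0.7. At 70% adherent, power was 87% and 80% continuous against 73% and 64% binary (losses 14 and 16). At 20% adherent it was 88% and 76% against 69% and 59% (losses 19 and 17).

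**The case against.** The strongest reply is that the cut is the definition of adherence. The Adherence section adopts both rules as definitions, eligibility excludes men who already meet the MVPA guideline, and the progression criterion is most naturally read as a proportion. A logistic GEE answers that question directly. Mean MVPA minutes measure volume: a man going from 155 to 400 minutes raises the mean without changing his adherence. This stands. It is why the binary analysis should not be demoted, and why a reader who infers that the definitions are wrong goes further than the text allows.

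Second, continuous analysis is not absent. Total MVPA and sedentary time are to be examined, and fitness, itself named as an adherence measure, goes into linear mixed models at all five visits. Proportions adherent are also estimated over time. A reader might infer that decline after the programme would go unseen; these provisions rule that out. They do not close the gap, because fitness is a proxy for activity and nothing ties total MVPA to an arm contrast or a predictor.

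Third, there is no power target to erode, and every power figure rests on assumed effects and a normal scale, whereas MVPA minutes may well be skewed. This also stands. A loss as large as 33 points can be produced, but only at a single visit and with a cut that few men pass. The planned repeated-measures arm comparison did not reach it.

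The statement that the analysis will not focus on group differences is no defence. It belongs to the efficacy outcomes; the adherence paragraph expressly compares groups.

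**Conclusion.** The point holds as a cheap improvement, not as an error that undermines the trial. For accelerometer-based adherence, the article names only logistic models on two cuts for arm contrasts and predictors, and leaves the continuous measures without a model.

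The firmest statement of size is relative efficiency: about 0.64, 0.58 and 0.49 at 50%, 70% and 80% adherent, for one measurement on a normal scale. In power terms, the four-visit arm comparison loses roughly 8 to 22 points under assumed effects of 0.5 to 0.7 SD at a two-sided 5% level, and less for small effects. Because the sample size rests on precision, lost precision is the better reading. Skewed activity data would change these figures.

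On importance, the Background lists adherence and its predictors as a primary aim and the abstract calls long-term adherence secondary, so a flat claim that a primary aim is compromised would be too strong. Adherence can nevertheless help decide whether an arm goes forward.

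**What to change.** In the Statistical analysis section, add a linear mixed model or Gaussian GEE for weekly MVPA minutes and another for mean steps per day. Use the same visits, group-by-time terms and predictors as the adherence models, and use them for arm contrasts and predictors. Provide for a transformation or robust standard errors if the data are skewed.

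Keep the two binary definitions and their logistic GEE for the proportions adherent with 95% confidence intervals, the 70% criterion and the 7,500-step sensitivity analysis.

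The cost is a few extra models and some wording, with no new data, visits or participants. The downsides are the handling of skewed data, and coefficients in minutes or steps that describe activity volume and not attainment of the guideline. The two sets of results should be labelled accordingly.

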**Design:**

Men diagnosed with prostate cancer, starting or continuing on androgen deprivation therapy for at least 6 months, fluent in English, and living close to one of two experienced Canadian study centers are eligible. Participants complete five assessments over one year, including a fitness assessment and self-report questionnaires. Socio-demographic and clinical data collection occur at baseline, bone mineral density testing at two time points, and blood work is performed at three time points. Participants are randomized in a 1:1:1 fashion to supervised personal training, supervised group training, or home-based smartphone- and health coach-supported training. Each participant receives a detailed exercise manual, including illustrations of exercises and safety precautions. Participants are asked to complete 4 to 5 exercise sessions per week, incorporating aerobic, resistance and flexibility training. Participant intensity levels will be monitored. The intervention duration is 6 months, with 6 months additional follow-up. Outcomes include: body composition, fitness testing, quality of life and fatigue, biological outcomes, and program adherence. Cost information will be obtained using patient diary-based self-report.

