**Quality of life**						
FACT-G (primary)	8-10 min	●	●	●	●	●
FACT-P	4-5 min	●	●	●	●	●
FACT-F	5 min	●	●	●	●	●

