### QOL and fatigue

Functional Assessment of Cancer Therapy – General (FACT-G) is used to assess general health-related QOL [32], whereas the FACT-P (Functional Assessment of Cancer Therapy - Prostate) evaluates prostate-specific QOL [33] and the FACT–F (Functional Assessment of Cancer Therapy – Fatigue) is used to evaluate cancer-related fatigue [34]. All three questionnaires are validated and have been widely used in cancer research measures, and in particular, in RCTs of exercise in men on ADT [14].

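### Fatigue (FACT-F) is left out of the modelled efficacy outcomes and the analysis is steered towards variances, although aim 2 needs efficacy estimates and a choice of phase III primary outcome

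*Protocol article*

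**What the plan says.** All references are to the protocol article.

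- **Aims, end of Background.** Aim 2 is "To obtain preliminary efficacy estimates for (a) group-supervised in-centre, and (b) home-based (smartphone-assisted) supported exercise programs", with 1:1 supervised training as the comparator, "for the clinical outcomes of QOL and physical fitness, and to select a primary outcome for a subsequent phase III trial".
- **Abstract, Design.** "Outcomes include: body composition, fitness testing, quality of life and fatigue, biological outcomes, and program adherence".
- **Table 1, Quality of life block.** FACT-G, FACT-P and FACT-F are listed together, each at all five visits. The first carries a tag, "FACT-G (primary" (closing bracket omitted here).
- **QOL and fatigue.** FACT-F is described beside the other two scales and "is used to evaluate cancer-related fatigue".
- **Statistical analysis.** "Quality of Life (FACT-G and FACT-P), musculoskeletal fitness, and aerobic fitness are efficacy outcomes". They are fitted with a linear mixed model that has subject-level random effects and group-by-time terms. The emphasis is placed away from arm differences and on "estimation of measures of within and between-person variance".
- **Criteria to move forward to phase III RCT.** At least 80% of clinical outcomes must be captured. An arm may be dropped if it does worse on, among other things, quality of life and fitness results.

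**The concern.** Two statements in the analysis section do not fit the aim that they serve.

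First, the list of efficacy outcomes names two of the three scales that Table 1 groups under quality of life and omits the third. Fatigue is not peripheral here. The Background lists it first among the common side effects of ADT and cites a randomised trial in which it improved with exercise.

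Second, aim 2 calls for efficacy estimates against 1:1 training, while the analysis is directed to variance components. Those are needed to size a phase III trial. They do not say whether an outcome moved during the six months, or how far group or home-based training differs from 1:1 on it.

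At stake is how well informed the phase III choice is. If the section is followed literally, FACT-F enters that choice with no modelled estimate, and the listed outcomes may be reported mainly through their variances. The primary tag on FACT-G adds an ambiguity, because the article does not say whether it refers to this trial or to the next.

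**Working it through.** **1. Inputs.** From Sample size calculation/power: 30 per arm, 90 in total, 10% drop-out, 100 recruited. From the criteria for moving forward: 70% retention as the minimum. Assumed, because the article gives no such figures: the standardised changes in step 5, and the one-sided alpha, power and margins in step 4.

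**2. The plan's own figure.** 90 / (1 − 0.10) = 100, which matches. The 30 per arm rests on guidelines for phase II trials, so no formula can be reproduced for it.

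**3. Precision for the estimates that aim 2 asks for**, in SD units of the quantity compared:
- One arm mean, n = 30: t(0.975; 29) / √30 = 2.045 / 5.477 = ±0.37 SD.
- Difference between two arms: t(0.975; 58) × √(2/30) = 2.002 × 0.258 = ±0.52 SD.
- The same difference with 70 of 100 men retained, about 23 per arm: t(0.975; 44) × √(2/23) = 2.015 × 0.295 = ±0.59 SD.
- An SD, from √(df/χ²): 0.80 to 1.34 times the estimate with one arm (29 df), and 0.87 to 1.17 times when pooled over three arms (87 df).

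So variances are estimated fairly well and arm contrasts roughly. Both can be had for every outcome, FACT-F included.

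**4. What variances can and cannot decide.** For a non-inferiority comparison of means with true difference zero, n per arm = 2(1.96 + 0.84)² / (margin/SD)². At one-sided alpha 0.025 and 80% power (assumed) this gives 393, 175, 99 and 63 per arm for margin/SD of 0.2, 0.3, 0.4 and 0.5. The ratio has no units, so outcomes on different scales can be compared once each has a margin. But two outcomes with equal SDs and equal margins give the same n even if one rises by 0.5 SD over six months and the other does not move. That information lies in the mean changes and contrasts.

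**5. Precision of a standardised change.** With standard error √(1/n + d²/(2n)), where d is the mean change divided by its SD:
- n = 90, d = 0.4: √(0.0111 + 0.0009) = 0.110, interval ±0.21.
- n = 70, d = 0.4: √(0.0143 + 0.0011) = 0.124, interval ±0.24.
- n = 90, d = 0.1: interval −0.11 to 0.31. For d = 0.5: 0.28 to 0.72.

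Even values as far apart as 0.1 and 0.5 give separate intervals that just overlap, although a comparison within the same men could be sharper. These estimates inform a choice but will not rank close candidates.

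**The case against.** The strongest reply is that little is actually lost.

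- The model has group-by-time terms, so it yields changes and arm contrasts for each listed outcome. Not focusing on arm differences is a matter of emphasis. The criteria for moving forward also use outcome capture and quality-of-life and fitness results. This stands: a reader might infer that variances are the only output, and the article does not say so.
- A reader might infer that variances in FACT points, oxygen uptake and repetitions cannot be compared, or that the choice cannot be made on evidence. Step 4 answers the first, since margin/SD and within/between variance ratios are unit-free. Step 3 answers the second, since the data allow estimates for every candidate. A detailed selection rule may properly sit in the full protocol or SAP, so its absence from an article is no fault.
- Aim 2 names quality of life and physical fitness, and the abstract names fatigue separately from quality of life. Leaving out FACT-F is therefore a flat contradiction only if FACT-F counts as quality of life. Table 1 groups it so, but the text elsewhere is less clear. This narrows the point without removing it: fatigue remains a named outcome, measured five times, beside two sibling scales that are modelled.
- A reader might take the tag on FACT-G to mean that the phase III choice is already made. It may simply mark the main quality-of-life measure of this trial, so it is an ambiguity only.
- Nothing shows that fatigue would respond best or that FACT-G would barely move. The Background cites quality-of-life gains with exercise, and also a study with no difference in fatigue between groups.
- All three arms exercise, so change from baseline mixes training with time on ADT and cannot isolate the response to training. This stands and limits how such a change may be described.

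**Conclusion.** The point holds as a mismatch between aim 2 and the analysis section. The explicit list of efficacy outcomes omits FACT-F, one of three scales in Table 1's Quality of life block. The stated emphasis on variance also plays down the efficacy estimates that the same article promises. An unseen SAP might settle both, but the published statements would still disagree.

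Its size is modest. The data are collected and the model would yield the estimates, so what is at risk is a less informed phase III choice, not an impossible one. The estimates would be exploratory: about ±0.52 SD for a two-arm contrast with 30 per arm, about ±0.59 SD if retention falls to the 70% minimum, and about ±0.21 for a pooled standardised change, assuming that change is near 0.4 with 90 men. The conclusion that FACT-F belongs among the candidates rests on Table 1's grouping and on the abstract's naming of fatigue as an outcome.

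**What to change.** 1. In Statistical analysis, add FACT-F to the outcomes fitted with the mixed model.
2. For each candidate (FACT-G, FACT-P, FACT-F, VO2peak, sit-to-stand, grip strength), report the baseline-to-6-month change, raw and standardised, and the group versus 1:1 and home-based versus 1:1 contrasts, all with 95% confidence intervals. Set them beside the variance components and the completeness of each measure, and label the table exploratory.
3. Describe change from baseline as training plus time on ADT, because there is no arm without exercise.
4. Add a note to Table 1 that the primary tag on FACT-G does not pre-empt the phase III choice.

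The cost is one further model, one table and a few sentences. No visit, questionnaire or patient burden is added. The drawback is that the contrasts will have wide intervals, so the text should warn against reading them as evidence of non-inferiority or inferiority.
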